**Fig. 2 Fig2:**
[figure not shown]
Gastrectomy and lymph node dissection in the conventional D2 procedure. The proximal margin of gastrectomy should achieve at least 3 cm for T2 or deeper tumors with an expansive growth pattern or 5 cm for those with an infiltrative growth pattern. The lymphadenectomy should include 1, 3, 4sb, 4d, 5, 6, 7, 8a, 9, 11p, and 12a groups of lymph nodes [3]

Patients in the D2 + CME group receive standardized LADG with D2 + CME [15], which is performed by the founder of this procedure. The standard D2 + CME procedure should meet the following criteria:Clearly exposing five mesogastrium (left gastroepiploic mesentery, right gastroepiploic mesentery, left gastric mesentery, right gastric mesentery, and postgastric mesentery)*En bloc* separation of the mesentery from the mesenteric bedDissecting along the root of the mesenteryLigation should reach the root of the blood vessels.After the mesentery is dissected, the lower side of the mesogastrium should be flat and smooth.

Before and after mesentery dissection, two photographs will be taken individually in each mesogastric area to evaluate the integrity of the mesenteric excision (Fig. 3).

**Fig. 3 Fig3:**
[figure not shown]
**a** Diagram of resected mesogastrium (*yellow*) during D2 + CME. **b** Intraoperative photographs show the standard procedures of mesenteric excision: (**1**) expose the mesogastrium clearly, (**2**) separate the mesentery from the mesenteric bed, (**3**) dissect along with the root of the mesentery, and (**4**) ligation should reach the root of the blood vessels. **c** Pictures of each mesogastrium were photographed under laparoscopy before (*left*) and after dissection (*right*) during D2 + CME. *LGEM* Left gastroepiploic mesentery, *RGEM* Right gastroepiploic mesentery, *LGM* Left gastric mesentery, *RGM* Right gastric mesentery, *PGM* Postgastric mesentery. *Black arrow* = mesogastrium [14]l

#### Postoperative management and adjuvant chemotherapy

Gastrointestinal function is evaluated twice per day; the gastric canal will be pulled out, and a liquid diet will be suggested beginning after the first flatus is confirmed. If patients are fully tolerant of a liquid diet for 4 days, they can begin a soft diet. Adjuvant chemotherapy will be started at the fourth or fifth week after surgery without contraindication [17].

All the patients in this trial are recommended to receive adjuvant chemotherapy. The first-line regimen is XELOX (oxaliplatin 130 mg/m^2^ on day 1 and capecitabine 1000 mg/m^2^ twice daily on days 1–14 of a 3-week cycle for eight cycles in 6 months). After each cycle, the toxicity of chemotherapy is graded according to the Nation Cancer Institute’s Common Terminology Criteria for Adverse Events (version 4) [18]. If grade 3 or 4 toxicity occurs, chemotherapy will be delayed up to 3 weeks, until the patient recovers from the adverse effects. When a patient experiences serious side effects and cannot tolerate the treatment, the drug dose should be reduced or chemotherapy could be stopped completely. Once a patient’s chemotherapy regimen is changed, the reason should be recorded.

### Surgeons and surgical quality control

Surgeons who will participate in this study will meet the following criteria: (1) have performed at least 100 cases of laparoscopic distal gastrectomy with D2 lymphadenectomy and (2) have performed at least 50 gastrectomies annually. These criteria qualified eight surgeons to participate in this study. Among them, seven surgeons who have had no training in the D2 + CME procedure are assigned to the D2 group, and the remaining one, who is the founder of the D2 + CME procedure, performs operations in the D2 + CME group.

Surgical quality control is evaluated by using intraoperative video recordings and the resection margin of the specimens. The extent of gastrectomy and lymph node dissection is based on the Japanese gastric cancer treatment guidelines (2010, version 3) [3]. In the D2 group, the intraoperative videos should clearly show the lymph dissection of stations including 1, 3, 4sb, 4d, 5, 6, 7, 8a, 9, 11p, and 12a. Furthermore, the dissected specimen should be checked by an experienced surgeon or a pathologist to ensure that the proximal resection margin and the removal of lymph nodes are satisfactory (Additional file 2). In the D2 + CME group, under the premise of meeting D2 qualification, the operative procedure should also be under the quality control of CME. Quality control of CME is based mainly on the intraoperative video recordings. In the D2 + CME procedure, the resection of the left and right mesogastria, the left and right gastroepiploic mesogastria, and the posterior mesogastrium should be clearly shown (Fig. 3). Furthermore, a mesenteric scoring system that includes the following parameters is applied for each of mesenteric region: trijunction point exposure (exposure of the incision of the mesentery), mesogastrium body (smooth and shiny surface of mesentery after resection), smooth plane of the surgical bed after mesenteric resection, and high tie ligation of the vessel. According to the quality of surgery, each parameter is scored as 2 (good), 1 (moderate), or 0 (poor) (Additional file 3). Then, the parameter scores are summed to get the mesenteric score. Considering that the posterior mesogastrium is short and often lacks blood supply, we simply score it as 2, 1, or 0. The scores of the operation should be recorded in a formal table (Additional file 4) and analyzed. In a standard D2 + CME surgery, the sum of the mesenteric scores should be at least 30.

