**Discussion:**

Previous studies have demonstrated the safety and feasibility of D2 + CME for locally advanced gastric cancer; however, there is still a lack of evidence to support its therapeutic effect. Thus, we performed this randomized trial to investigate whether D2 + CME can improve oncologic outcomes of patients with locally advanced gastric cancer. The findings from this trial may potentially optimize the surgical procedure and may improve the prognosis of patients with locally advanced gastric cancer.

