### Sample size

This study was designed to evaluate the superiority of D2 + CME compared with D2 alone in terms of DFS. The sample size is calculated through two independent proportions power analysis. The calculated sample size is 304 (152 per group), with a two-sided α of 5% and an 80% statistical power (z-test) to detect a supposed 3-year DFS difference of 15% (60% in D2 group vs. 75% in D2 + CME group). Considering potential withdrawals, an additional 10% of patients will be investigated to guarantee that the final sample size is large enough. Therefore, the planned sample size is 336 (168 per group). The enrollment period will last for 3 years.

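### Surgeon is completely confounded with arm (founder versus seven others), so the trial can compare two surgeon-plus-procedure packages but cannot credit a DFS difference to D2 + CME itself

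*Protocol article*

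**What the plan says.** The protocol article's section on surgeons and surgical quality control sets minimum experience and volume criteria, which eight surgeons met. Seven, with no training in D2 + CME, "are assigned to the D2 group, and the remaining one, who is the founder of the" D2 + CME procedure, operates in the other arm. The Operative approach section says the same from both sides: D2 operations are done by experienced surgeons not trained in D2 + CME, and of the D2 + CME operation it says "which is performed by the founder of this procedure". No section describes a surgeon operating in both arms.

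Randomization is 1:1 at patient level (Trial design). On size, the article states: "The sample size is calculated through two independent proportions power analysis". The inputs are "60% in D2 group vs. 75% in D2 + CME group", "with a two-sided α of 5% and an 80% statistical power (z-test"). The primary comparison is a log-rank test (Statistical analysis).

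The aim, under Study aims and objectives, is whether D2 + CME is superior to conventional D2 on 3-year DFS. The abstract's Discussion asks whether D2 + CME "can improve oncologic outcomes of patients with locally advanced gastric cancer". The Interim analysis section attributes lower bleeding (23.87 vs 39.72) and a higher node harvest (34.31 vs 25.73) to the D2 + CME procedure. The Discussion does not mention that surgeon and arm coincide.

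**The concern.** Randomizing patients balances patients between arms. It does not balance surgeons, because the surgeon follows automatically from the arm. With one surgeon on one side, seven on the other and no overlap, any difference between the founder's results and those of the other seven that is unrelated to CME enters the estimated effect of CME in full.

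This is a feature of the stated design, not a detail that an analysis plan could supply. No covariate, stratification or random effect can split two factors that never vary separately. At stake is the primary conclusion. A significant log-rank test would be read as evidence for an operation that other surgeons could adopt, when the data support only a statement about one surgeon performing it. The interim text already makes that attribution for bleeding and nodes.

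**Working it through.** **1. The plan's own figure.** Inputs from Sample size: 60% and 75%, two-sided alpha 5%, power 80%. The mean proportion is 0.675. With the pooled-variance z-test,

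n = [1.96·√(2·0.675·0.325) + 0.8416·√(0.60·0.40 + 0.75·0.25)]² / 0.15² = 151.9, so 152 per group.

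This reproduces the stated figure: "The calculated sample size is 304 (152 per group"). The 10% allowance gives 304 × 1.10 = 334 or 304 / 0.9 = 338, so the planned 336 is consistent. Power is 80.0% at 152 per group and 83.8% at 168. The calculation is correct for independent patients.

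**2. What the calculation leaves out for the procedure question.** Let s be the between-surgeon SD of true 3-year DFS. Assume equal caseloads for the seven D2 surgeons (168 / 7 = 24 each) and treat the founder as a draw from the same distribution. Then

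Var(difference) = 2·0.675·0.325/168 + s²·(1 + 1/7).

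The first term is 0.002612 (SE 0.0511), which is all that the planned test uses. The protocol gives no value for s, so the values below are assumptions.

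| Assumed s | s²·8/7 | Total variance | SE | Type I error of the nominal 5% test | Power with matching SE |
|---|---|---|---|---|---|
| 2 points | 0.000457 | 0.003069 | 0.0554 | 7.1% | 77% |
| 3 points | 0.001029 | 0.003640 | 0.0603 | 9.7% | 70% |
| 5 points | 0.002857 | 0.005469 | 0.0740 | 17.6% | 53% |

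Type I error = 2·[1 − Φ(1.96·0.0511/SE)]. Power = Φ(0.15/SE − 1.96).

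As a cross-check, a beta-binomial simulation of one cluster of 168 against seven of 24 was run at an intraclass correlation of 0.01 (SD about 4.9 points at 60% DFS). It gave a type I error of 16.5%, against 16.1% by formula.

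**3. More patients would not remove it.** The term s²·(1 + 1/7) does not depend on the number of patients. At s = 5 points, the 95% half-width cannot fall below 1.96·0.05·√(8/7) = 10.5 points, against a target difference of 15.

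**4. The same problem as a fixed bias.** If the founder is not exchangeable with the others, the issue is an unknown shift. Suppose CME has no effect and the founder's patients would do better than 60% by a fixed amount under any technique. At 168 per arm, the chance of a significant result is 8.7% for a 3-point advantage, 15.7% for 5 points, 48.5% for 10 points and 83.8% for 15 points. These advantages are assumptions too.

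**5. What a tipping point would look like.** Suppose the observed difference were exactly 15 points at 168 per arm.
- Fixed founder advantage that removes significance: 0.15 − 1.96·0.0511 = 0.050, about 5 points.
- Between-surgeon SD that removes significance: √{[(0.15/1.96)² − 0.002612]·7/8} = 0.053, about 5.3 points.

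**The case against.** A reader might infer that the sample size, alpha or power is wrongly stated. The documents do not support that. The figure of 152 reproduces exactly, and 5% and 80% are valid for the founder doing D2 + CME against these seven doing D2. Treating providers as fixed in a single-center trial is a legitimate modelling choice. This part of the objection stands, and it limits the point to attribution.

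The inflated error rates rest on an assumed SD. All eight surgeons meet the same thresholds (at least 100 laparoscopic D2 distal gastrectomies and at least 50 gastrectomies a year), follow one guideline, and have video and specimen checks. This could well make s small. But minimum thresholds and adherence checks do not show that outcomes are equal, and the founder's own component cannot be estimated from this trial. The figures are illustrations, not estimates.

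The exchangeability assumption is also open to challenge, since the founder may be atypical. That is fair, and it is why the fixed-shift calculation is given as well.

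The arrangement has a rationale: D2 surgeons untrained in CME cannot carry its technique into the control arm. The trade-off is real, but it does not restore the ability to attribute a difference to the procedure.

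A reader might also suspect different perioperative teams, or that the operating surgeon is not recorded. Neither is supported. Postoperative management is described once for all patients, patients and follow-up staff are masked, and a condensed article cannot show what the dataset lacks. Nor do the documents show that the founder gets better results for reasons other than CME; they only leave that possibility open.

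Finally, the article poses benefit as a question, describes its findings as potentially useful and calls for more trials. That softens the general claim, but the aim and the interim text still speak of the procedure.

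**Conclusion.** The point holds as a limit on what the trial can conclude. Surgeon and arm are fully confounded by design, so neither a DFS difference nor the interim bleeding and node differences can be assigned to D2 + CME as a procedure. The stated alpha and power are correct for the package comparison. For the procedure they would hold only if surgeons did not differ in DFS. How far they would be off is unknown. The range of about 7% to 18% type I error and 77% down to 53% power depends on assumed SDs of 2 to 5 points, equal D2 caseloads, an exchangeable founder and the use of 3-year proportions. The confounding itself depends on none of these assumptions. It governs the primary conclusion and deserves correction before the DFS evaluation.

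**What to change.** Enrollment closed on 28 June 2018, so the allocation of surgeons cannot change. Two changes remain open.

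1. Restate the objective, the power statement and the conclusion as D2 + CME performed by its founder versus conventional D2 performed by seven surgeons not trained in CME. Make no claim for the procedure alone, state the confounding as a limitation, and word the interim bleeding and node results in the same way.

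2. Before the 2021 DFS evaluation, pre-specify a tipping-point sensitivity analysis. It should report how large a founder advantage in 3-year DFS, or what assumed between-surgeon SD over a fixed range, would remove significance. Show DFS by surgeon in the D2 arm descriptively.

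The tipping-point analysis should not rest on a between-surgeon variance estimated from the seven. In simulation, with seven surgeons of about 24 patients each, an ANOVA estimate truncated at zero came out as exactly zero in about 55%, 52% and 43% of trials at true SDs of 2, 3 and 5 points. An interval built on it would often be no wider than the unadjusted one.

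The cost is wording and one extra analysis. The downside is a narrower claim.

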### Withdrawal

All the patients are freely informed to participate in this study and can decide to withdraw from this trial at any time. If a patient withdraws, his/her information will not be recorded in this study. However, the research team can still collect outcome data from the healthcare records. Patients provide informed consent that their personal data held by this study can be freely withdrawn; otherwise, these data will be retained.

### Outcome measures

#### Primary endpoint

Three-year DFS will be evaluated in 2021. Once a patient dies, the death date, cause of death, and how the death was identified will be entered on the case report form (CRF). Once a subject is lost after the last follow-up, the patient’s survival data will be collected by communicating with the patient or with his/her family via telephone or letter.

#### Secondary endpoints

*Recurrence patterns*: Recurrence will be assessed by routine follow-up. The recurrence location and time will be recorded when diagnosed. The recurrence date, site, and pattern, as well as how the recurrence is diagnosed, are recorded on the CRF. The recurrence pattern is classified into six categories: locoregional, lymphatic, peritoneal, hematogenous, mixed, and unclassified. Locoregional recurrence includes tumor recurrence in the anastomosis, gastric stump, and adjacent tissue, including gastric bed, porta hepatis, regional lymph nodes (perigastric, left gastric, common hepatic, celiac, and hepatoduodenal), as well as the adjacent abdominal wall. Lymphatic recurrence includes tumor recurrence in distant lymph nodes, including para-aortic, inguinal, postperitoneal, Virchow’s nodes, and other distant sites. Peritoneal recurrence is defined as peritoneal seeding or Krukenberg tumor. Hematogenous recurrence means that the tumor relapses in the liver, lung, bone, brain, or other distant organs. A mixed pattern includes those recurrences that meet more than one of the above categories. Suspected recurrence, which lacks imaging or endoscopy evidence, falls in the unclassified recurrence pattern category.*Morbidity and mortality*: Postoperative morbidity and mortality are evaluated within 30 days after operation. All the complications are diagnosed on the basis of either clinical examination or symptoms. Anastomosis-related complications, such as anastomosis bleeding, leakage, and stenosis, will be confirmed by endoscopy, abdominal CT, gastrointestinal X-ray imaging, or angiography. Abdominal abscesses will be proven by ultrasonography or a CT scan that reveals the presence of septic fluid in the abdominal cavity, with the patient’s temperature higher than 38 °C for more than 24 hours. Intraoperative and postoperative hemorrhage will be defined as an amount of bleeding more than 300 ml. Pancreatic injury will be diagnosed by an increase in serum amylase level more than three times the upper limit of normal and obvious clinical symptoms. Lymphatic leakage will be confirmed by a positive chyle test when the patient’s abdominal drainage fluid is more than 300 ml/d for 5 continuous days after operation. Intestinal fistula will be confirmed by the presence of a bowel-to-bowel or a bowel-to-cutaneous fistula tract via fistulogram. Intestinal obstruction will be diagnosed by the lack of a bowel movement for more than 5 days after surgery; a simple x-ray examination will show mechanical obstruction with air-fluid level or paralytic ileus. Other complications, such as diarrhea, lymphorrhea, urinary tract morbidities, and respiratory morbidities, should be diagnosed by corresponding clinical symptoms and examinations. The severity of postoperative complications will be assessed according to the Clavien-Dindo classification [19]. In addition, 90-day postoperative mortality data will also be collected and analyzed to evaluate the short-term outcome of the operation.*Intraoperative complications*: Intraoperative complications will be evaluated during operation. Intraoperative complications will be defined as hemorrhage caused by named vascular injury, visceral organ injury, mechanical factor-related injury, cardiopulmonary dysfunction due to hypercapnia, and others.*Cost-effectiveness*: The total in-hospital cost will be assessed. The two groups will be compared with regard to cost-effectiveness. Information related to cost (e.g., length of hospital stay, complications, comorbidity) will be collected and evaluated.

The timing of our enrollment, intervention, and outcome measurements are summarized in Fig. 4.

**Fig. 4 Fig4:**
[figure not shown]
Schedule of enrollments, interventions, and assessments

### Sample size

This study was designed to evaluate the superiority of D2 + CME compared with D2 alone in terms of DFS. The sample size is calculated through two independent proportions power analysis. The calculated sample size is 304 (152 per group), with a two-sided α of 5% and an 80% statistical power (z-test) to detect a supposed 3-year DFS difference of 15% (60% in D2 group vs. 75% in D2 + CME group). Considering potential withdrawals, an additional 10% of patients will be investigated to guarantee that the final sample size is large enough. Therefore, the planned sample size is 336 (168 per group). The enrollment period will last for 3 years.

### Randomization, masking, and data collection

All the eligible patients will be registered in this study and randomized to either the D2 + CME group or the D2 group (1:1) on the basis of a computer-generated randomization list (generated using SAS version 9.2 software; SAS Institute, Cary, NC, USA) with a block size of 6. Patient enrollment and randomization will be performed by an independent data collection group (managed by the Department of Epidemiology and Biostatistics, Huazhong University of Science and Technology). The data collection group will then collect patient information and fill out the CRF, including general characteristics, preoperative staging, operative findings, pathological reports, and postoperative outcomes. All the data will be placed into the local database via a data registry server managed by the data collection group. In this trial, the patients and the follow-up staff are masked to the treatment allocation.

### Statistical analysis

A statistical analysis plan will be developed and agreed upon by the data collection group. In summary, the continuous data will be presented as the mean ± SD and will be statistically analyzed with Student’s *t* test or the Wilcoxon rank-sum test. The categorical variables will be compared between the D2 and D2 + CME groups by the χ^2^ test or Fisher’s exact test. Grade data, including age, ASA score, and Clavien-Dindo classification, will be compared with the Wilcoxon signed-rank test. The survival curves for 3-year DFS (primary endpoints) and OS will be estimated via the Kaplan-Meier method and will be compared by log-rank test. All the *p* values are based on two-sided statistical tests; *p* < 0.05 is considered statistically significant.

Two interim analyses will be planned in this trial. The first interim analysis will be planned for the date at which half of the planned sample size has been enrolled to assess the safety of this study. The second will be held when the entire planned sample size has been enrolled. The stopping criteria in the study protocol are as follows:

1. Complication rate and mortality in the D2 + CME group are significantly higher than those in the D2 group, leading to study termination owing to the unsafety of the CME procedure

2. Survival in the D2 + CME group is significantly superior to that of the D2 group, leading to study termination owing to the efficacy of the CME procedure

3. Survival in the D2 + CME group is significantly poorer than that of the D2 group, leading to study termination owing to futility of the CME procedure

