**Methods/design:**

A single-center, prospective, parallel-group, randomized controlled trial of laparoscopic distal gastrectomy with D2 + CME versus conventional D2 was conducted for patients with locally advanced gastric cancer at Tongji Hospital, Wuhan, China. In total, 336 patients who met the following eligibly criteria were included and were randomized to receive either the D2 + CME or D2 procedure: (1) pathologically proven adenocarcinoma; (2) 18 to 75 years old; cT2–4, N0–3, M0 at preoperative evaluation; (3) expected curative resection via laparoscopic distal gastrectomy; (4) no history of other cancer, chemotherapy, or radiotherapy; (5) no history of upper abdominal operation; and (6) perioperative American Society of Anesthesiologists class I, II, or III. The primary endpoint is 3 years of disease-free survival. The secondary endpoints are overall survival, recurrence pattern, mortality, morbidity, postoperative recovery course, and other parameters.

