### Trial design

This is a prospective, controlled, randomized single-center trial evaluating the therapeutic effect of laparoscopic distal gastrectomy with D2 + CME versus conventional D2 in 336 patients with gastric cancer. Randomization is at the patient level. Participants are randomized 1:1 to receive either D2 + CME or D2.

This study is designed to evaluate the superiority of D2 + CME compared with D2 alone in terms of DFS. We are supposing differences in 3-year DFS of no less than 15% (60% in D2 vs. 75% in D2 + CME) as demonstrating superiority.

Patients enrolled in this trial are asked to complete at least 3 years of follow-up after operation. Then, with allowance, follow-up will last for 5 years. Follow-up is at 3-month intervals for the first 2 years and at 6-month intervals for the last 3 years. At every follow-up, the patients will undergo a physical examination; their nutritional status will be assessed; and blood tests (including blood count, liver function test, tumor markers) will be performed. Abdominal computed tomography (CT) and endoscopy will be performed twice annually. The date and site of the first recurrence, as well as the date of death, will be recorded. The study flow diagram is shown in Fig. 1, and the Standard Protocol Items: Recommendations for Interventional Trials (SPIRIT) checklist is provided in Additional file 1.

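### The protocol names a paired test (Wilcoxon signed-rank) for comparing age, ASA score and Clavien-Dindo grade between two independent arms; probably a slip for the rank-sum test, and confined to baseline and secondary comparisons

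*Protocol article*

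**What the plan says.** The Statistical analysis section of the protocol article assigns tests by type of variable:

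- Continuous data: Student's t "test or the Wilcoxon rank-sum test". Both are tests for independent samples.
- Categorical data: "The categorical variables will be compared between the D2 and D2 + CME groups" by a χ² or Fisher's exact test, again for independent samples.
- Ordinal data: "Grade data, including age, ASA score, and Clavien-Dindo classification, will be compared with the Wilcoxon signed-rank test". This is a paired test.
- DFS and OS: Kaplan-Meier curves and a log-rank test.

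The design is described consistently as unpaired. The Abstract (Methods/design) calls it "A single-center, prospective, parallel-group, randomized controlled trial of laparoscopic distal gastrectomy". Trial design says "Randomization is at the patient level" and "Participants are randomized 1:1 to receive either D2 + CME or D2". The Sample size section uses a calculation for two independent proportions. The randomization section describes a computer-generated list with a block size of 6 and mentions no matching.

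**The concern.** The signed-rank test ranks the differences within pairs and asks whether they are centred on zero. Without pairs there are no differences to rank. Age is a single baseline value, and neither ASA nor Clavien-Dindo is described as a before-and-after comparison within a patient. Nothing in the design gives the test a meaning for these three variables.

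This is a positive statement about three named variables, so it is not a detail left to the analysis plan. An analysis plan written from this summary would inherit it. Anyone carrying it out literally would have to drop patients or invent a pairing, and two analysts could then report different p values from the same data. The variable for which this matters most is Clavien-Dindo grade, the stated measure of complication severity under the secondary endpoint of morbidity and mortality.

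**Working it through.** **1. Confirm that the arms are independent, using the plan's own figures.**

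Sample size, with 60% against 75% 3-year DFS, two-sided α of 0.05 and 80% power (Sample size section). With pooled proportion 0.675:

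n per arm = [1.960·√(2·0.675·0.325) + 0.842·√(0.60·0.40 + 0.75·0.25)]² / 0.15² ≈ 152

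This gives 304 in total, as stated, from a formula for independent samples.

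Interim morbidity, 11 of 82 against 15 of 83 (Interim analysis section). Uncorrected χ²:

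χ² = 165·(11·68 − 71·15)² / (82·83·26·139) = 165·317² / 24,596,884 ≈ 0.674, so p = 0.412

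This matches the stated p value and is also an independent-samples test.

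**2. Look for any implied pairing.** Under 1:1 allocation a block of 6 holds three patients per arm. That balances numbers but does not match individuals: even inside one block there are 3! = 6 ways to pair them.

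**3. Unequal arms.** With 82 and 83 patients there is no one-to-one pairing. A standard signed-rank routine given arrays of these lengths returned an error.

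**4. Equal arms, arbitrary pairing.** The documents give no grade distributions, so those below are assumptions. Each scenario used 168 per arm (the planned size), 3,000 replicates and a two-sided 0.05 level. Clavien-Dindo was coded as none plus four grades.

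| Scenario (assumed) | Signed-rank rejects | Rank-sum rejects |
|---|---|---|
| Clavien-Dindo, both arms 82/6/7/4/1% | 5.1% | 4.6% |
| Clavien-Dindo, 82/6/7/4/1% vs 72/10/10/6/2% | 47% | 58% |
| ASA I/II/III, both arms 30/60/10% | 4.8% | 4.7% |
| ASA I/II/III, 30/60/10% vs 20/62/18% | 77% | 77% |

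The Monte Carlo standard error at 5% is √(0.05·0.95/3000) ≈ 0.4 percentage points, so both tests hold their nominal level. The power loss appears for Clavien-Dindo and not for ASA. In the second Clavien-Dindo scenario the expected share of arbitrary pairs with equal grades is 0.82·0.72 + 0.06·0.10 + 0.07·0.10 + 0.04·0.06 + 0.01·0.02 ≈ 0.61. The signed-rank test as run discards those pairs.

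**5. Dependence on patient order.** Three datasets were drawn from the second Clavien-Dindo scenario, and one arm of each was re-ordered 3,000 times.

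| Dataset | Rank-sum p | Signed-rank p, lowest to highest | Median |
|---|---|---|---|
| 1 | 0.040 | 0.008 to 0.057 | 0.027 |
| 2 | 0.743 | 0.775 to 1.000 | 0.961 |
| 3 | 0.111 | 0.101 to 0.368 | 0.245 |

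In dataset 1, 99.9% of orderings fell below 0.05, so crossing the threshold was possible but rare. The general result is that the p value is not fixed by the data and can sit well away from the rank-sum value.

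**6. Trace where the named test is used.** Age and ASA are baseline characteristics. Clavien-Dindo grades severity within a secondary endpoint. The first stopping criterion refers to complication rate and mortality, and the other two refer to survival. DFS and OS use the log-rank test. None of these calls on the signed-rank test.

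**The case against.** The strongest reply is that this is a naming slip that nobody would carry out. The rank-sum test is named two sentences earlier. The Interim analysis section also reports no significant differences in age and ASA between 82 and 83 patients, which a signed-rank test could not have produced without dropping someone. That suggests an unpaired test was used in practice. This reply largely stands and is the most likely explanation. It does not remove the point: the two tests are named separately for different kinds of data, and the document does not say which test produced the interim comparisons.

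The case against a large effect also stands. Baseline p values carry little inferential weight in a randomized trial, so the real reach is one secondary severity comparison.

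A reader might infer three stronger things that the documents or the check do not support:

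- *The safety judgement is compromised.* The stopping criterion uses complication rate and mortality, not grade. The interim judgement rested on 11 of 82 against 15 of 83, with a p value that an ordinary χ² test reproduces, and on zero mortality in both arms. No Clavien-Dindo comparison is reported there.
- *The test gives invalid results in the sense of excess false positives.* Under arbitrary pairing, type I error was about 5% in both null scenarios.
- *Age is certainly misclassified.* Listing it with ordinal data may mean that age groups are intended; the text does not settle this.

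**Conclusion.** The statement is wrong as written: a paired test is assigned to comparisons between two independent arms. It cannot be computed on unequal arms, and on equal arms its p value depends on an arbitrary ordering of patients. Under the assumed distributions it costs about 11 percentage points of power for Clavien-Dindo (58% to 47%) and none for ASA, without inflating type I error. The inapplicability follows from the design alone; the sizes rest on assumed grade distributions and would change with others. The reach is two baseline comparisons and one secondary comparison. Minor to moderate correction.

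**What to change.** In the Statistical analysis section, replace the Wilcoxon signed-rank test with the Wilcoxon rank-sum (Mann-Whitney) test for ASA score and Clavien-Dindo classification. Analyse age under the rule already given for continuous data, or state the age groups if it is to be treated as ordinal. A proportional-odds model for the two ordinal variables is an option, not a need. It would also help to confirm which test produced the interim age and ASA comparisons.

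The cost is one sentence in the protocol, carried into the analysis plan. The sample size of 304 (336 with the allowance for withdrawals), data collection and the primary analysis do not change.
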